## Abstract

**Background:**

Substance use is highly prevalent among Dutch adolescents. The Healthy School and Drugs program is a nationally implemented school-based prevention program aimed at reducing early and excessive substance use among adolescents. Although the program's effectiveness was tested in a quasi-experimental design before, many program changes were made afterwards. The present study, therefore, aims to test the effects of this widely used, renewed universal prevention program.

**Methods/Design:**

A randomized clustered trial will be conducted among 3,784 adolescents of 23 secondary schools in The Netherlands. The trial has three conditions; two intervention conditions (i.e., e-learning and integral) and a control condition. The e-learning condition consists of three digital learning modules (i.e., about alcohol, tobacco, and marijuana) that are sequentially offered over the course of three school years (i.e., grade 1, grade 2, and grade 3). The integral condition consists of parental participation in a parental meeting on substance use, regulation of substance use, and monitoring and counseling of students' substance use at school, over and above the three digital modules. The control condition is characterized as business as usual. Participating schools were randomly assigned to either an intervention or control condition.

Participants filled out a digital questionnaire at baseline and will fill out the same questionnaire three more times at follow-up measurements (8, 20, and 32 months after baseline). Outcome variables included in the questionnaire are the percentage of binge drinking (more than five drinks per occasion), the average weekly number of drinks, and the percentage of adolescents who ever drunk a glass of alcohol and the percentage of adolescents who ever smoked a cigarette or a joint respectively for tobacco and marijuana.

**Discussion:**

This study protocol describes the design of a randomized clustered trial that evaluates the effectiveness of a school-based prevention program. We expect that significantly fewer adolescents will engage in early or excessive substance use behaviors in the intervention conditions compared to the control condition as a direct result of the intervention. We expect that the integral condition will yield most positive results, compared with the e-learning condition and control condition.

**Trial registration:**

The protocol for this study is registered with the Nederlands Trial Register NTR1516

## Background

Dutch adolescents are one of the leaders in terms of drinking frequency and binge drinking in Europe and they usually start drinking in early adolescence [1]. Also, their use of tobacco and marijuana increases rapidly during this period [2]. This is worrisome in that early initiation of substance use has many detrimental consequences, such as distortion of brain development (e.g., [3]) and elevated risk for later dependence and misuse (e.g., [4]). Investigators and policy makers emphasize the importance of a delay in age of onset for preventing the adverse health consequences of early initiation of substance use.

The implementation of effective prevention programs is a potential powerful tool to lower the prevalence of substance use in early adolescents and to delay the age of onset of substance use. In the past, many school-based prevention programs have been developed and implemented [5-12]. In general, three major types of school-based interventions can be distinguished, namely knowledge, cognitive-affective, social influence, and alternative programs [6]. The knowledge programs aim to enhance students' knowledge on biological and psychological aspects of substance use in order to accomplish a more negative attitude towards substance use, which will deter actual use. The cognitive-affective programs argue that psychological factors place students in vulnerable positions and therefore aim to improve students' self-confidence and self-awareness. Finally, the social influence programs aim to improve social and/or life skills in order to prevent peer pressure leading to substance use. In the literature there is consensus on the fact that social influence programs seem to be most effective, in that they more often show positive effects compared to knowledge and affective programs [5,9,13,14]. Hence, previous studies showed that interactive methods sort more effect compared to non-interactive methods (e.g., [14,15]) in prevention of early and excessive substance use.

One of the most well-known and widely used universal prevention programs for Dutch early adolescents is 'The Healthy School and Drugs (HSD)' program. The HSD program combines elements of all three types of school-based prevention and is based on the ASE model [16-18], which is often used in predicting and explaining health behavior. The HSD program is annually implemented and carried out at approximately 60% of all secondary schools in The Netherlands, and is one of the few school-based Dutch prevention programs of which the effectiveness was studied in a quasi-experimental design [19]. The HSD program was mainly found to be effective on cognitive aspects (i.e., knowledge and attitude) of alcohol and tobacco use and less so on behavioral outcomes. Permanent improvement of the program and tuning to recent developments is essential and many changes were made in both materials (e.g., e-learning modules) and content (e.g., marijuana module) since the last evaluation. Hence, a recalibration of the effectiveness of the HSD program and its new materials seems necessary. Even more so, because the HSD program was never tested through a randomized controlled trial (e.g., [20]).

The HSD program is a multi-component prevention program aimed at reducing early and/or excessive substance use among adolescents. The program consists of four pillars, which are: information lessons (i.e., e-learning modules), parental participation, regulation of substance use, and monitoring and counseling of students' substance use. Although scholars argue that multi-component approaches, like the HSD program, are more effective than single component approaches (e.g., [15]) many Dutch schools do not want to invest time and resources in all components. To sort out if solely relying on the education of adolescents will have a preventive effect or that a multi-component approach of the HSD program is necessary in order to obtain such a preventive effect, we included an additional intervention condition (i.e., e-learning) in our study design.

### Aim and hypotheses

The primary aim of the 'Healthy School and Drugs' study is to assess the effectiveness of this multi-component universal prevention program by conducting a randomized clustered trial including 23 Dutch secondary schools. Three follow-up assessments (i.e., after 8, 20 and 32 months) will be carried out to examine the effects of the intervention conditions. Two hypotheses will be tested. First, in line with prior findings, we expect that the program will lead to a lower likelihood of unhealthy substance use behaviors. We expect that adolescents in the intervention conditions, relative to controls, will be less likely to engage in early or excessive substance use behaviors at follow-up. More specifically, we expect that this effect will be more pronounced in the integral condition compared to the control condition than in the e-learning condition compared to the control condition.

Second, following the ASE model, we expect that cognitive aspects of behavior will mediate the effects of the program. Specifically, we expect that adolescents included in the intervention conditions (as compared to controls) will (a) have more knowledge about the -harmful aspects of- specific substances, (b) have more negative and less positive attitudes towards substance use, (c) perceive to have less approval for using substances from their social environment, (d) have more confidence in refraining from use when confronted with tempting substance use offers, and (e) have more adequate risk perceptions concerning the consequences of substance use.

## Methods/Design

### Study design

The HSD effectiveness study is a 3-year randomized clustered trial (RCT) with three arms - two interventions (i.e., e-learning and integral) and a control condition - testing the prevention program effects. Participants are 3,784 early adolescents of 23 secondary schools from seven different regions in The Netherlands: 1,330 are involved in the e-learning condition, 1,195 in the integral condition, and 1,259 in the control condition. After initial recruitment and enrollment in the trial, randomization took place at the school level, to avoid contamination between conditions (e.g., [21]). Directly after conducting the randomization procedure, a baseline assessment will be carried out.

The HSD program will be implemented after the baseline assessment in different phases to prevent overburdening of schools. In the first year - when adolescents are around 12 years old - the focus in the integral condition will be on starting with the information lessons on alcohol and to get parents involved in the program. In the second year, the schools in the integral condition will implement the two remaining pillars besides the information lessons on tobacco. Finally, in the third year the information lessons on marijuana will be implemented (see Figure 1). The schools in the e-learning condition will solely implement the information lessons on alcohol, tobacco, and marijuana in respectively the first, second, and third year. Finally, participants in the control condition will carry on in the same manner, thus a 'business as usual' approach will be followed at these schools.

**Figure 1 F1:**
[figure not shown]
**Study design**.

Assessments in all three conditions will be conducted at baseline, after 8, 20, and 32 months. Participating schools receive the prevention program materials for free. Also, they receive school-based information about the substance use behaviors of their students after each assessment.

### Participants

#### Recruitment

The HSD program will be implemented in schools with the help of prevention departments of regional institutions for treatment and care of drug addiction (ITCD) and Municipal Health Services (MHS). Therefore, we contacted all these institutions to ask for corporation in the effectiveness trial. Seven institutions (i.e., VNN Friesland, VNN Groningen, VNN Drenthe, Centrum Maliebaan, GGD Zuid-Hollandse eilanden, Novadic-Kentron, and Mondriaan Zorggroep) agreed to take part in the study and secondary schools were recruited from these regions. All secondary schools in these regions were screened for eligibility. Exclusion criteria were recent involvement (i.e., parental participation in our target group, e-learning modules, regulation or monitoring and counseling activities in the past two years) in the HSD program and not offering a four-year education program. All eligible schools received an invitation letter and an information brochure and were contacted after two weeks to discuss participation in the study. Participants were thus recruited by school participation and all first grade students of participating secondary schools were included in the study. We visited the participating schools and during these visits further information was provided about the research project. In collaboration with the schools' headmasters, we informed the students' parents annually about the goals of the study by a letter in which parents were also notified that they could refuse participation of their child in the study. Thus, a passive informed consent procedure is followed in which parents (and their children) can refuse study participation by email, telephone or in person during the entire study period. Approval for the design and data collection procedures was obtained beforehand from the ethic committee of the Radboud University Nijmegen.

#### Randomization

Randomization occurred at the school level to avoid contamination between conditions. Thus, all first grade students from one school were allocated to the same condition (i.e., one of the intervention conditions or the control condition). An independent statistician performed the allocation before baseline assessment. Randomization was carried out centrally, using a blocked randomization scheme (block size 6) and stratified by level of education the schools offered.

### Sample size calculation

We estimated our targeted sample size based on a small effect size (*d*) of. 15 [22]. As the program has not been tested on effectiveness before, it is difficult to formulate an effect size. We based this on other prevention effectiveness studies on adolescent substance use, which generally have small effects [19]. We used the general-purpose statistical software package STATA to calculate the estimated sample sizes per condition. If a small effect occurs, then a sample size of N = 698 adolescents per condition is required at the end of the study for testing the hypothesis of superior effectiveness in a two-sided test at Alpha = 0.05 and a power of (1-Beta) = 0.80. We corrected this sample size for adolescents who will be lost in follow-up (e.g., changing schools, repeating grades) and for the fact that our data is clustered (i.e., adolescents are nested within schools). Considering these corrections, at least N = 1,061 adolescents per condition should be included to test the effectiveness of the HSD program. In accordance with the intention-to-treat principle, all adolescents randomized to a condition are included in further analyses testing the study hypotheses.

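### The 1,061-per-condition target gives 80% power for d = 0.15 only if the school ICC is about 0.003 or less, and the protocol states the power without that condition

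*Protocol article*

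**What the plan says.** The section on sample size calculation (Protocol article) sets a standardised effect of 0.15, tested "in a two-sided test at Alpha = 0.05 and a power of (1-Beta) = 0.80". From this it derives that "a sample size of N = 698 adolescents per condition is required at the end of the study".

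Two adjustments follow. One is for attrition: "We corrected this sample size for adolescents who will be lost in follow-up (e.g., changing schools, repeating grades". The other is "for the fact that our data is clustered (i.e., adolescents are nested within schools". The result after both is: "Considering these corrections, at least N = 1,061 adolescents per condition should be included to test the effectiveness of the HSD program".

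The Study design section gives the cluster structure: "Participants are 3,784 early adolescents of 23 secondary schools from seven different regions in The Netherlands", of whom 1,330 are in e-learning, 1,195 in integral and 1,259 in control. The Recruitment and Randomization sections confirm that schools are the units allocated and that every first-grade pupil of a school is included. The Statistical analyses section contrasts each intervention condition separately with control and adjusts for sex, educational level, age and ethnicity.

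**The concern.** Few schools, each contributing a large number of pupils, make power very sensitive to between-school variation. With about 165 pupils per school, an ICC of 0.01 multiplies the variance of a condition mean by about 2.6. The article allows a factor of only 1.52, and that factor must also cover pupils lost over 32 months.

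The article prints both ends of the adjustment (698 and 1,061) and the cluster structure. The largest ICC that the adjustment can absorb therefore follows from its own figures, whatever a fuller protocol may add.

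What is at stake is how the result is read. The article says that the findings will drive redevelopment of a programme used in about 60% of Dutch secondary schools. A reader who takes 80% power for d = 0.15 at face value would give a non-significant contrast more weight than the design may support.

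**Working it through.** **Inputs from the article:** d = 0.15; two-sided alpha 0.05; power 0.80; 698 and 1,061 per condition; 3,784 pupils in 23 schools; 1,195 integral, 1,259 control, 1,330 e-learning.

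**Assumed, because the article gives no value:** loss A = 0, 10% or 20%; school ICC over a range; equal school sizes; schools split evenly (23/3 = 7.67 per condition).

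**1. The article's base figure.** n = 2 × (1.960 + 0.842)² / 0.15² = 697.7, so 698. It reproduces.

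**2. Total inflation.** 1,061 / 698 = 1.520, for attrition and clustering together.

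**3. School size.** m = 3,784 / 23 = 164.5. If 1,061 pupils per condition were spread over 7.67 schools, m would be 138.

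**4. Largest ICC that the target absorbs.** After loss A, the room left for the design effect is 1.520 × (1 − A). Setting this equal to 1 + (m(1 − A) − 1) × ICC gives:

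| Loss | Room for design effect | Max ICC, m = 164.5 | Max ICC, m = 138 |
|---|---|---|---|
| 0% | 1.52 | 0.0032 | 0.0038 |
| 10% | 1.37 | 0.0025 | 0.0030 |
| 20% | 1.22 | 0.0017 | 0.0020 |

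For example, with no loss: 0.520 / 163.5 = 0.0032. At about 34% loss nothing is left for clustering (698 / 1,061 = 0.658).

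**5. Power at the enrolled sizes, integral vs control.** The effective size per condition is n(1 − A) / [1 + (m(1 − A) − 1) × ICC], with m = 164.5. Power = Φ(0.15 / √(1/n₁ + 1/n₂) − 1.960), using the two effective sizes.

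Worked example, ICC 0.01 and A = 0.2: pupils per school at follow-up are 131.6 and the design effect is 1 + 130.6 × 0.01 = 2.31. The effective sizes are 1,195 × 0.8 / 2.306 = 414.5 and 1,259 × 0.8 / 2.306 = 436.7. The ratio of effect to standard error is 2.19, and power is Φ(0.23) = 59%.

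| Assumed ICC | 0% loss | 10% loss | 20% loss |
|---|---|---|---|
| 0.003 | 86% | 84% | 80% |
| 0.005 | 79% | 76% | 73% |
| 0.01 | 63% | 61% | 59% |
| 0.02 | 44% | 43% | 42% |
| 0.05 | 23% | 23% | 23% |

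E-learning vs control (1,330 vs 1,259) is 1 to 2 points higher. Using a t reference because schools are few lowers power by about 2 to 4 points on 20 df (23 schools less 3 conditions). On about 13 df (the two conditions compared) it lowers power by about 2 to 7 points.

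**6. Largest ICC that still gives 80% at the enrolled sizes (z test).** About 0.005, 0.004 and 0.003 at 0, 10 and 20% loss.

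**7. Limit set by the number of schools.** As pupils per school grow, the effective size per condition tends to 7.67 / ICC. This cannot reach 698 once the ICC exceeds 7.67 / 698 = 0.011, so above that value adding pupils in the same schools does not restore 80% power.

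**The case against.** The strongest reply is that the article gives no ICC and no attrition rate, so no shortfall is demonstrated. A reader might infer that 23 schools cannot deliver 80% power for d = 0.15, or that every realistic school ICC defeats the calculation. The article supports neither inference. Nothing in it says what ICC to expect, and 1,061 cannot be called an arithmetical error, only a figure that requires a small ICC.

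Other parts of the reply also stand:

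- The target is worded as a minimum and enrolment exceeded it. At an ICC of 0.003 the enrolled groups still have 80 to 86% power by the z test.
- Randomisation was stratified by level of education and the analysis adjusts for it. The ICC that matters is the one left after adjustment, which may be smaller than the crude one. Unequal school sizes would work in the other direction.
- An article condenses a fuller protocol, so unstated inputs are not in themselves a fault.
- The article does not say that a non-significant result will be read as no effect. That risk is about readers, not about a planned rule.

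What the reply does not remove is that the two published figures and the published cluster structure fix how much clustering the target can carry. That amount is very small, and the power statement is made without the condition.

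**Conclusion.** The point holds in conditional form. The base of 698 is correct. The allowance from 698 to 1,061 supports 80% power for d = 0.15 only if the school ICC is at most about 0.003 with no loss (0.0038 if school size is taken as 138), about 0.0025 to 0.0030 with 10% loss and about 0.002 with 20% loss. At the enrolled sizes the limit for integral vs control is about 0.005 with no loss, falling to 0.003 with 20% loss.

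If the adjusted ICC is 0.005, 0.01, 0.02 or 0.05, power over 0 to 20% loss is about 73-79%, 59-63%, 42-44% or 23%, and somewhat lower with a t reference. These values rest on assumed ICC and loss, equal school sizes and an even split of schools. They show how sensitive the claim is; they do not estimate this trial's power.

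**What to change.** Do not enrol more. Replace the unconditional statement of 1,061 and 80% with a calculation for 23 schools of about 165 pupils that shows its inputs:

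- the school ICC for each primary outcome, estimated from the baseline data after the planned covariates, including educational level;
- the attrition rate assumed to 32 months;
- an allowance for few schools of unequal size.

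Report the resulting power for d = 0.15, or the effect detectable with 80% power, for each intervention condition against control. If power is below 80%, add that a non-significant result does not exclude d = 0.15. The percentages tabulated above should not be copied into the plan as results, because they come from assumed ICC and loss values.

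The cost is a short calculation on data already collected and a reworded paragraph. The downside is that the stated power will probably become less favourable.

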### Study intervention

#### Healthy School and Drugs program

The HSD program is a multi-component, school-based prevention program aimed at reducing excessive and early substance use among adolescents. The program for secondary schools consists of four pillars, which are:

1) Information lessons (e-learning modules): e-learning modules were developed for the information part of the program. These digital modules connect well to the experience of adolescents. Students work through the modules in their own pace during biology or counselor lessons, or in a special project week. The lessons pay attention to knowledge, attitude, and behavior with regard to substance use. Besides tutoring the students about the risks concerning substance use, students are also prepared for coping with group pressure by training their refusal skills. The modules consist of small films, animations, and several types of interactive tasks and identification is a central part of the modules. Also, adolescents are able to discuss relevant topics or to exchange their opinions through chat rooms and forums. Students receive three modules: alcohol (4 lessons), tobacco (3 lessons), and marijuana (3 lessons) in the first, second, and third grade, respectively. The lessons and modules are designed to gradually increase adolescent's skills in responsibly dealing with substances. Teachers are trained in the content and operation of the digital modules before the lessons are offered to the students.

2) Parental participation: Parents of first grade students are invited to attend a parental meeting in which information will be provided about the HSD prevention program and the relevant substances. Also, parents will be informed throughout a parental brochure and the school newsletter. The parental meeting will be held at school in collaboration with the ITCD or MHS. The duration of the parental meeting will be approximately 90 minutes. First, in a brief opening the attention of parents is captured by facts on substance use in adolescence. Then, brief information on the school regulation on substance use is provided. Characteristics and risks of substance use, opinions on substance use, and education in the home setting with respect to substance use will be discussed in the remainder of the meeting.

3) Regulation: the idea behind this pillar of the program is that rules set boundaries and create clarity. Therefore, the school needs to set an adequate regulation standard and rules concerning substance use behaviors of students and personnel. If the school lacks such regulation a special team will be instigated, including all relevant parties (e.g., parents, students, teachers, direction). This team will create or revise the rules and will plan how to communicate and maintain the rules in and around school. The school team will be assisted by the ITCD or MHS during this process.

4) Monitoring and counseling: An operation protocol (if absent) is to be formulated on how to deal with problematic substance use behaviors among students. Also, the ITCD or MHS will provide a training session on signaling and guiding problematic substance use among individual students. This training is meant for teachers, mentors, student speculators, and the care coordinator(s) of the school. During this training session practical information will be provided on how to recognize problematic use in students and on how to efficiently support these students. Further, advice will be given on how to use the operation protocol in daily practice.

